## Abstract

**Background:**

Neuromuscular electrical stimulation (NMES) is an established therapy that has been widely used for many decades to improve circulation in the legs. However, studies using NMES devices in an elderly, ambulant, and otherwise apparently healthy population are lacking; this is despite the use of such devices being indicated for lower leg symptoms (such as aches, pain, and cramps) that are frequently seen in older individuals. The main purpose of this study is to evaluate the effect of non-invasive foot NMES (administered using Revitive Medic^©^) on such symptoms compared to a sham in a 12-week period.

**Methods:**

This is a single-center, single (participant)-blind, parallel-group, randomized, placebo-controlled (sham group), interventional study. Participants will be randomized to 1 of 3 groups (1:1:1) with each study group receiving a different type of foot NMES: Revitive sham; Revitive Medic^©^ Program 1; or Revitive^®^ Program 2. Each participant will be instructed to self-administer the foot NMES device for 30 min twice daily for 8 weeks. During the study, all participants will continue with their normal life, activities, medications, and diet with no restrictions. Following the 8-week NMES treatment program participants will be assessed for Canadian Occupational Performance Measure performance (COPM-P) and satisfaction (COPM-S) scores, lower leg pain, lower leg symptoms (heaviness, tiredness, aching and cramps), and blood flow volume and intensity.

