### Outcomes {12}

The primary endpoint for the study comprises a comparison of change in Canadian Occupational Performance Measure Performance (COPM-P) score from baseline to Week 8 for Revitive Medic^©^ Program 1 versus Revitive sham. COPM-P score is a self-evaluation measure of each participant’s current physical/ occupational performance status.

Secondary endpoints comprise:Change in COPM-P from baseline to week 12, comparing Revitive Medic^©^ Program 1 versus Revitive sham.Change in COPM-P from baseline to weeks 8 and 12 comparing Revitive^®^ Program 2 and Revitive sham.Change in Canadian Occupational Performance Measure Satisfaction (COPM-S) score from baseline to week 8, comparing Revitive Medic^©^ Program 1 versus Revitive sham and Revitive^®^ Program 2 versus Revitive sham. COPM-S score is a self-evaluation measure of each participant’s current satisfaction with their relevant physical/occupational performance.Change in leg pain from baseline to weeks 8 and 12, comparing Revitive Medic^©^ Program 1 versus Revitive sham and Revitive^®^ Program 2 versus Revitive sham; participants will rate leg pain using an 11-point numerical rating scale.Change in blood flow volume and intensity from baseline during device use, comparing Revitive versus Revitive sham.Change in symptom score from baseline to weeks 8 and 12 in terms of overall symptom score and each item (heaviness, tiredness, aching, and cramps), comparing Revitive Medic^©^ Program 1 versus Revitive sham and Revitive^®^ Program 2 versus Revitive sham.

Assessments conducted at the different study visits are presented in Table 1.

**Table 1 Tab1:** Study assessments in the NMES stimulation trial

	**Telephone assessment (≥ week − 1)**	**Baseline assessment** **(week 0)**	**Treatment period**	**Week 8**	**Week 12**
Eligibility	x	x			
Randomization	x				
Informed consent		x			
Demographics		x			
Medical history	x	x	x	x	x
Medications	x	x	x	x	x
Device issue and familiarization		x			
Device usage		x	x	x	
COPM		x		x	x
Symptom (heaviness, aching, tiredness, and cramps) scores		x		x	x
Leg pain		x		x	x
Doppler ultrasound		x		x^a^	
Adverse events		x	x	x	x

^a^For participants with poor quality Doppler data at week 0

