Following the 8-week intervention period, participants will return their device to the research team and will be assessed for Week 8 outcome measures. Participants will then return for a repeat assessment of all outcome measures at Week 12, following a 4-week follow-up period without device use. This post-intervention follow-up period is included to assess the short-term maintenance of the treatment effect.

Safety assessment comprises a formal evaluation of all adverse events (AEs), adverse events of special interest (events with a potential causal association to the use of the study device), and serious adverse events (SAE).

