**Fig. 1 Fig1:**
[figure not shown]
Design of the NMES stimulation trial

Potential participants who express an interest in the study will be contacted by telephone and provided with further information about the study, any questions will be answered and initial screening assessments conducted to inform on eligibility. Once an interested participant is deemed suitable for the study, they will be sent the participant information sheet, randomized, and an appointment will be made to attend the baseline visit; the baseline visit will be arranged for after the participant has had sufficient time to consider the participant information sheet (at least 2 days). Potential participants will be provided with an opportunity to ask questions and request further information about the study at the baseline visit; the participant will also have eligibility criteria checked and provide informed consent. Subsequent procedures will only be initiated once the participant has provided written informed consent.

The participant will undergo baseline assessments and be allocated their study device. Participants will then be instructed as to the correct use of their device and undergo a Doppler assessment of deep leg blood flow volume and intensity both before and during device use. Participants will be sent home with their device to use over the 8-week treatment period.

Participants will return to the study center after 8 weeks (at the end of the treatment period) for study assessments and to return their study device; they will remain on-study for another 4 weeks (follow-up period) during which time they will not use the device. Participants will return to the study center for week 12 assessments, after which they will be considered as having completed the study.

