## Data collection and management

### Plans for assessment and collection of outcomes {18a}

Outcome and baseline trial data will be collected using a case report form administered by the investigator at each study visit. Images and data from the Doppler ultrasound will be acquired electronically at the baseline visit.

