#### Deep leg blood flow volume and flow intensity

Deep leg blood volume will be assessed using Doppler ultrasound before and during the use of the Revitive device [36]; the IsoRocker on the Revitive device will be disabled during Doppler ultrasound, to minimize movement during assessment. Blood flow will be measured at the medial aspect of the ankle between the medial malleolus and the Achilles tendon, using the appropriate arterial ultrasound probe and pre-set volume flow algorithms on a duplex ultrasound machine. Two sets of recordings will be taken, pre-stimulation and 30 s into Waveform 5. Five seconds worth of data will be recorded at each time. The recording will then be broken down into individual frames, saved onto the scanner, and analyzed mathematically by MATLAB [36]. MATLAB analysis of frames determines peak flow volume and the peak intensity of flow within those 5 s. If baseline visit data are of insufficient quality due to noise, Doppler ultrasound can be repeated at week 8.

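### Blood flow is presented as an outcome after the 8-week programme and again at week 12, but Doppler is an acute baseline measurement whose noisy recordings may be replaced by week-8 ones

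*Protocol article*

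**What the plan says.** Two places present blood flow as a follow-up outcome.

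- Abstract, Methods: "Following the 8-week NMES treatment program participants will be assessed for" COPM scores, leg pain, "lower leg symptoms (heaviness, tiredness, aching and cramps), and blood flow volume and intensity".
- Outcomes {12}, below Table 1: "Participants will then return for a repeat assessment of all outcome measures at Week 12".

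The operative sections describe an acute measurement.

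- The secondary endpoint in Outcomes {12} is "Change in blood flow volume and intensity from baseline during device use, comparing Revitive versus Revitive sham". It names no week, whereas the COPM, pain and symptom endpoints all do.
- Participant timeline {13}: at the baseline visit participants "undergo a Doppler assessment of deep leg blood flow volume and intensity both before and during device use".
- Plans for assessment and collection of outcomes {18a}: "Images and data from the Doppler ultrasound will be acquired electronically at the baseline visit".
- Table 1 marks Doppler at week 0, and at week 8 with the footnote "For participants with poor quality Doppler data at week 0". The week-12 column has no mark.
- The section on deep leg blood flow under {18a} sets two recordings in one session, one before stimulation and one 30 s into Waveform 5, and adds: "If baseline visit data are of insufficient quality due to noise, Doppler ultrasound can be repeated at week 8".

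The deep leg blood flow section under Statistical methods {20a} then keeps whichever recording is judged cleaner, and it pools the two active programs into one group. Who will be blinded {17a} says that the assessor at the blood flow measurement would know whether the device is active or sham.

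**The concern.** There are two separate problems.

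The first is what the result can be said to show. Improved circulation is the mechanism that the article offers for symptom relief. A reader who relies on the abstract would take the flow result as an effect of 8 weeks of treatment. The scheduled measurement can only show what happens to flow while the device is running.

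The second is what the acute contrast contains. Randomisation protects the comparison of active with sham at first use. Once some values come from a later visit, chosen after randomisation on a quality judgement made where allocation is known, the contrast may combine responses before and after a course of treatment, in proportions that could differ by arm.

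**Working it through.** **Timing: the sections compared**

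| Place | Baseline visit | Week 8 | Week 12 |
|---|---|---|---|
| Abstract, Methods | not mentioned | blood flow listed | not mentioned |
| Outcomes {12}, text on week 12 | – | – | all outcome measures |
| Outcomes {12}, endpoint | during device use, no week named | no | no |
| Table 1 | yes | only if week 0 was poor | no |
| Participant timeline {13} | yes, before and during use | not mentioned | not mentioned |
| {18a}, deep leg blood flow | yes, two recordings in one session | optional repeat if noisy | not mentioned |

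The endpoint, the schedule and the measurement section agree with one another. The abstract and the week-12 sentence are the outliers.

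A randomised comparison of flow after the programme would need week-8 readings in both arms on an unselected set of participants. The only week-8 readings planned are in participants selected for poor week-0 images.

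To show what such a subset could detect, take 39 sham and 78 pooled active participants (Sample size {14}: 39 per group) and an assumed share *f* scanned at week 8 in each arm. At two-sided 5% significance and 80% power:

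minimum detectable difference = (1.960 + 0.842) × √(1/n + 1/(2n)) SD, with n = 39*f*.

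- *f* = 100%: n = 39, 2.802 × √(1/39 + 1/78) = 0.55 SD
- *f* = 30%: n = 11.7, 1.00 SD
- *f* = 10%: n = 3.9, 1.74 SD

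The subset would be too small as well as selected.

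**Replacement: possible size**

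Exposure before a week-8 recording is at most 8 weeks × 7 days × 2 sessions = 112 sessions.

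Let *f* be the share of active-arm values taken at week 8, and *d* the difference in SD between the week-8 and first-use acute responses in active participants, with no such difference in sham. The shift in the active-minus-sham contrast is *f* × *d*.

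| | d = 0.25 | d = 0.5 | d = 1 |
|---|---|---|---|
| f = 10% | 0.025 | 0.05 | 0.10 |
| f = 20% | 0.05 | 0.10 | 0.20 |
| f = 30% | 0.075 | 0.15 | 0.30 |

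The document gives neither *f* nor *d*, so every value of both in this table is assumed. The shift is zero if no scan is replaced or if the acute response does not change over the 8 weeks.

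**The case against.** The strongest reply is that this is a slip in an abstract. The body defines an acute endpoint consistently, and both the abstract's own discussion paragraph and the main Discussion speak of circulation during use. That reply stands to this extent: the trial sets no 8-week circulatory endpoint, so it has not failed to deliver one. A reader might infer a design failure, but the documents support only a misstatement of what is measured and when.

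On replacement, the reply is that a repeat is optional and limited to noisy scans. It also appears to be a before-and-during pair from one session, so each participant remains their own control. The endpoint wording says during device use and does not say first use. All of this is fair, and it makes the mixing conditional. It does not remove it, because the acute response itself may change after a course of treatment.

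Three stronger readings are tempting and are not supported.

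- *Week-8 recordings are made at a higher intensity.* The intervention description lets participants raise the setting to keep a strong but comfortable level. The article does not give the setting used for a week-8 Doppler.
- *Noise, and so replacement, is more frequent in active legs because they contract.* The rocking function is disabled during scanning to limit movement, but nothing reports or predicts noise by arm.
- *The quality judgement is known to be biased.* The assessor at the measurement knows the device type, and the rule states no noise criterion. That leaves room for unequal replacement without showing that it occurs. The article does not say who makes the judgement.

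The objection that dropping noisy week-0 scans could itself cause selection, if unreadable scans differ by arm, also stands. The fix has to allow for it.

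**Conclusion.** The timing contradiction holds on the text alone and needs no assumption. The abstract and the week-12 sentence conflict with the endpoint, Table 1 and the measurement sections, and no randomised comparison of blood flow after 8 weeks of use is planned.

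The replacement problem holds as a possibility of unknown size. Under the assumed shares of 10% to 30% and differences of 0.25 to 1 SD, it moves the acute contrast by 0.025 to 0.30 SD, and it may be nil. That calculation rests on a changed response in active participants and none in sham.

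Blood flow is a secondary outcome. The primary COPM-P comparison is not touched by either problem. The point is still worth correcting, because it governs what may be concluded about circulation and the correction is cheap.

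**What to change.** 1. Correct the abstract to say that blood flow is an acute outcome, measured before and during device use at the baseline visit, and is not an effect of the 8-week programme.
2. Correct the week-12 sentence in Outcomes {12} so that it excludes Doppler, in line with Table 1.
3. Limit the blood-flow conclusion to the acute response under the conditions measured: one waveform, with the rocking function disabled.
4. Base the main blood-flow summary on week-0 recordings. Report the number of unreadable and of replaced scans by arm.
5. Give the analysis that includes week-8 repeats, labelled by visit, as a sensitivity analysis.

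The cost is wording and one rule for the analysis set; no extra scans are needed. The main summary would have somewhat fewer evaluable recordings, and it could be subject to selection if unreadable scans differ by arm. For that reason both analyses, and the counts by arm, should be shown.

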**Discussion:**

Revitive^®^ foot NMES has been proven to increase blood circulation in the legs during use, which may help to relieve symptoms such as pain, heaviness, cramps, and tiredness. When NMES is applied to the plantar surface of the feet it indirectly induces contraction of the calf muscle, activating the musculo-venous pump and thus improving circulation. This study aims to provide data informing on the applicability of foot NMES for the management of leg symptoms that are likely to be indicative of poor circulation in an elderly (> 65 years) community population.

**Trial registration:**

ISRCTN10576209.

## Administrative information

Note: the numbers in curly brackets in this protocol refer to SPIRIT checklist item numbers. The order of the items has been modified to group similar items (see http://www.equator-network.org/reporting-guidelines/spirit-2013-statement-defining-standard-protocol-items-for-clinical-trials/).

## Introduction

### Background and rationale {6a}

Lower leg symptoms such as aching/pain, leg heaviness, tiredness, and cramping are common in older adults and impact considerably on physical functioning and quality of life. A consequential deterioration in physical functioning due to lower leg symptoms is often considered part of the normal aging process [1]. Functional limitation is multifactorial in origin but, in part, reflects self-restriction of activity to reduce the occurrence of leg discomfort [2]. However, these lower leg symptoms can develop due to prolonged inactivity, a sedentary lifestyle, and restricted movement/activity due to medical circumstances. Associations between pain, low levels of physical activity, and physical limitation have led to the development of a “vicious cycle” model in which leg symptoms limit physical activity; in turn limitation of activity levels increases the severity of leg symptoms [3]. Such symptoms can indicate poor blood flow to the legs [1, 4–6].

Peripheral artery disease is a condition that occurs because of the development of atherosclerotic lesions that limit blood flow to the legs. Reduced blood flow because of peripheral artery disease is associated with a number of physiological manifestations in the lower extremities including vascular dysfunction, altered muscle metabolism, impaired angiogenesis, and inflammatory activation all of which contribute to symptoms of limb discomfort and functional limitation [2]. It is thought that spending prolonged periods of time in a static or sedentary position not only contributes to reduced blood flow but also exacerbates the development of atherosclerotic lesions, as blood flow exerts shear stress across the endothelial surface [7].

The traditional symptom of peripheral artery disease is intermittent claudication, whereby limited flow of oxygenated blood to the legs causes pain on walking that resolves with rest [8]; definitive diagnosis however requires demonstration of low ankle brachial index [1]. Most patients with peripheral artery disease do not present with intermittent claudication: 20% to 50% are reported with no exertional leg symptoms; and 40% to 50% report atypical leg symptoms such as pain/discomfort at rest, pain/discomfort that does not cause them to stop walking, or pain/discomfort that does not resolve with rest [1]. Some individuals with peripheral artery disease report no exertional leg symptoms but may restrict their physical activity as an avoidance mechanism.

It is widely understood that peripheral artery disease is underdiagnosed, in part because of the variety of leg symptoms associated with the condition but also because asymptomatic disease occurs in up to 60% of patients [9]. The prevalence and significance of low normal and abnormal ankle brachial index in a community-dwelling population of sedentary, older individuals is largely unknown. In the LIFE study which considered more than 1566 community-dwelling, sedentary individuals aged 70 to 89 years, 14% of participants were identified as having peripheral artery disease based on ankle brachial index; 16% had borderline peripheral artery disease, 33% had low normal ankle brachial index, and 37% had no peripheral artery disease. This highlights that peripheral artery disease is common among the community-dwelling population of sedentary-older population but is often undiagnosed. Low ankle brachial index was associated with older age and poorer mobility in terms of 400-m walk time and 4-m walk velocity [10].

NMES is an established therapy that has been widely used for many decades as a treatment for muscle impairment associated with various musculoskeletal, neurological, and vascular conditions [11]. It involves the repeat application of a low-level electrical current to facilitate muscle contraction. NMES programs are typically composed of a sequence of stimulation-rest cycles across a range of frequencies and intensities to generate repeated muscle contraction [12]. When NMES is applied to the plantar surface of the feet it indirectly induces contraction of the calf muscle which: activates the musculo-venous pump, increases arterial and venous flow and microcirculation, reduces venous stasis, increases interstitial hydrostatic pressure, promotes interstitial tissue fluid reabsorption, increases lymphatic flow and improves muscle tone [13–19]. Improved circulation delivers more oxygenated blood to the legs, feet, and ankles and helps maintain leg circulatory health, while regular muscle stimulation increases muscle strength to help improve mobility.

Foot NMES devices have been demonstrated to boost blood circulation [20–22] in the legs thereby relieving symptoms such as aching/pain, heaviness, tiredness, and cramps. In healthy individuals, NMES application to the feet using the Revitive footplate significantly increased median lower limb arterial and venous blood flow during the procedure [23]. Subsequent studies of NMES using the Revitive footplate in individuals with peripheral artery disease showed significant increases in blood volume flow and time-adjusted mean blood velocity during device use; this was associated with amelioration of claudication symptoms during exercise, increased exercise capacity, and improved disease-specific quality of life [24]. Similarly, studies in patients with chronic venous disease demonstrate that NMES significantly increases venous flow parameters and ameliorates the effect of orthostasis on fluid accumulation during use [25, 26].

This study aims to investigate the effects of non-invasive NMES delivered via a footplate device (Revitive Medic^©^) on lower leg blood flow and symptoms in community-dwelling adults over the age of 65 years.

The study will consider the effects of NMES delivered by two Revitive Medic^©^ programs in comparison with sham treatment; Revitive Medic^©^ Program 1 uses an NMES program of 15 waveforms that runs twice over 30 min to stimulate blood flow in the feet and lower legs; Revitive^®^ Program 2 comprises 6 waveforms delivered in a package of 10 that is run 3 times over 30 min.

### Objectives {7}

The primary objective of the study is to evaluate the efficacy of non-invasive foot NMES administered using Revitive Medic^©^ Program 1 over 8 weeks compared with Revitive sham. The secondary objective is to evaluate the efficacy of non-invasive foot NMES administered using Revitive^®^ Program 2 over 8 weeks compared with Revitive sham.

### Trial design {8}

This is a single-center, single (participant)-blind, parallel-group, randomized, placebo-controlled (sham group), interventional study. Participants will be randomized to 1 of 3 groups (1:1:1) with each study group receiving a different type of NMES:Group 1—Revitive shamGroup 2—NMES using Revitive Medic^©^ Program 1Group 3—NMES using Revitive^®^ Program 2.

Each participant will be instructed to self-administer the foot NMES device for 30 min twice daily over 8 weeks. Treatment will be administered in a seated position with the participant placing the soles of their feet onto the rubberized foot plates. The device is timed to run continuously for 30 min.

A hierarchical testing approach will be used with comparison of Revitive sham versus Revitive Medic^©^ Program 1 as the primary endpoint; if a statistically significant difference is seen for the primary endpoint, Revitive sham versus Revitive^®^ Program 2 will be tested as a secondary endpoint. The study will investigate if Revitive Medic Program 1 is “superior” compared to Sham, and if that is true, then will go on to investigate if Revitive Program 2 is ‘superior’ compared to Sham.

